#### ***Secondary outcomes***

– To assess the recording of cardiovascular risk in electronic medical records, the REGISTER variable will be calculated: number of patients with no history of cardiovascular disease (primary prevention) treated with statins without having any record of a cardiovascular risk calculation.

– To assess the economic impact of prescriptions, the COST variable will be calculated: the total cost of all prescriptions for new cholesterol-lowering drugs in primary prevention reimbursed by the national health system that are considered inadequate during the study period.

The intervention is designed to produce an increase in the REGISTER variable and a decrease in the COST variable.

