**Methods:**

This nonblinded, cluster-randomized clinical trial analyzes data from primary care electronic medical records (ECAP) and other databases. Inclusion criteria are patients aged 35 to 74 years with no known cardiovascular disease and a new prescription for cholesterol-lowering drugs during the 2-year study period. Dependent variables include the following: RETIRA, defined as new cholesterol-lowering drugs initiated during the year preceding the intervention, considered inadequate, and withdrawn during the study period; EVITA, defined as new cholesterol-lowering drugs initiated during the study period and considered inadequate; COST, defined as the total cost of inadequate new treatments prescribed; and REGISTER, defined as the recording of cardiovascular risk factors. Independent variables include the GP’s quality-of-care indicators and randomly assigned study group (intervention vs control), patient demographics, and clinical variables. Aggregated descriptive analysis will be done at the GP level and multilevel analysis will be performed to estimate the intervention effect, adjusted for individual and GP variables.

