#### ***Secondary objectives***

1. To describe demographic and clinical characteristics of patients receiving new prescriptions for cholesterol-lowering drugs.

2. To determine the degree of adequate prescription of cholesterol-lowering drugs in patients treated for primary prevention (i.e., without previous history of cardiovascular disease).

3. To identify the factors associated with adequate prescription of cholesterol-lowering drugs in primary prevention.

4. To analyze the degree to which cardiovascular risk is recorded in electronic medical records after the intervention.

5. To determine the economic impact of the cholesterol-lowering drugs prescribed for primary prevention during the study period.

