#### ***Primary outcomes***

The primary study variable is improved prescription adequacy in the use of cholesterol-lowering drugs for primary prevention of cardiovascular disease according to the recommendations of ICS clinical practice guidelines, comparing the intervention group to usual clinical practice.

Two dependent variables will be analyzed to address the primary objective:

RETIRA, defined as new cholesterol-lowering drugs initiated during the year preceding the intervention, considered inadequate, and no longer prescribed after the GP receives feedback information. This variable is directly affected by the intervention because patient records included in the calculation of this variable will be precisely those that triggered the intervention feedback.

EVITA, defined as new cholesterol-lowering drugs initiated during the 12 months follow-up period and considered inadequate.

Improved prescription adequacy is defined as an increase in the RETIRA variable and decrease in the EVITA variable.

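### REGISTER counts statin-treated patients without a recorded risk, so avoiding statins in unrecorded patients (or withdrawing them, if treated means currently treated) lowers it with no change in risk recording

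*Protocol article*

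**What the plan says.** Secondary objective 4 of the protocol article is this: "To analyze the degree to which cardiovascular risk is recorded in electronic medical records after the intervention". Under Secondary outcomes, REGISTER is the variable meant to serve it: "To assess the recording of cardiovascular risk in electronic medical records, the REGISTER variable will be calculated". The definition that follows is a bare count, the "number of patients with no history of cardiovascular disease (primary prevention) treated with statins without having any record of a cardiovascular risk calculation". It gives no denominator, no fixed cohort and no statement of whether treated means currently treated or ever treated in the period. The same section gives the expected direction: "The intervention is designed to produce an increase in the REGISTER variable and a decrease in the COST variable". The abstract describes the variable differently, with no restriction to treated patients: "REGISTER, defined as the recording of cardiovascular risk factors".

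Under Primary outcomes, the intended effect is a change in who is treated: "Improved prescription adequacy is defined as an increase in the RETIRA variable and decrease in the EVITA variable". RETIRA concerns new treatments "considered inadequate, and no longer prescribed after the GP receives feedback information". The other outcome is "EVITA, defined as new cholesterol-lowering drugs initiated during the 12 months follow-up period and considered inadequate". Under Outcomes, a treatment is adequate if REGICOR risk is at least 10% or LDL cholesterol is at least 240 mg/dl.

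**The concern.** REGISTER depends on two things at once: whether risk was recorded and whether the patient is on a statin. The second is a post-randomisation state that the intervention sets out to alter. A patient with no recorded risk and LDL below 240 mg/dl meets neither adequacy criterion. Many of the patients REGISTER counts are therefore ones whose treatment the feedback flags. If the GP does not start the statin, or stops it, and still records nothing, the count can fall.

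At stake is the interpretation of objective 4. A feedback programme that changed prescribing and left recording untouched could show a between-arm difference in REGISTER, and that difference would be reported as a change in risk recording.

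**Working it through.** The article gives no figure for REGISTER, so there is none to reproduce. The check is set logic followed by illustrations on stated assumptions.

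**1. Who is counted.** Combining the adequacy criteria with the REGISTER definition:

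| Patient on new treatment | Adequate? | In REGISTER? |
|---|---|---|
| Statin, no recorded risk, LDL below 240 | No | Yes |
| Statin, no recorded risk, LDL 240 or more | Yes | Yes |
| Statin, recorded risk below 10%, LDL below 240 | No | No |
| Statin, recorded risk 10% or more, within the 12-month window | Yes | No |
| Non-statin cholesterol-lowering drug | Either | No |

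Only the first row both attracts feedback and sits in REGISTER. Avoiding or stopping treatment in the third row, or a non-statin in the last, leaves the count unchanged.

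**2. Avoided starts (applies whether treated means current or ever).** Sample size gives about 60,000 new statin treatments a year, or 30,000 per arm at 1:1. Assumed: 50% of starts inadequate; half of those unrecorded; all unrecorded starts inadequate; 10% of inadequate starts avoided, in equal proportion among recorded and unrecorded.

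- Inadequate starts avoided: 30,000 × 0.5 × 0.10 = 1,500.
- REGISTER before: 30,000 × 0.5 × 0.5 = 7,500. After: 7,500 × 0.90 = 6,750, a fall of 10%.
- Of the 1,500 avoided treatments, 750 leave REGISTER. The number is 0, 375, 1,125 or 1,500 if the unrecorded share of inadequate starts is 0, 25%, 75% or 100%.
- If REGISTER pools both study years, first-year starters stay counted and the first year resembles the second, the count goes from 15,000 to 14,250, a fall of 5%.

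**3. Withdrawals (only if treated means currently treated).** Let N = 30,000 per arm, u the unrecorded share, w0 control-arm withdrawal, and d the extra withdrawal among unrecorded patients in the intervention arm, with identical recording.

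- Control count = N·u·(1 − w0). Intervention count = N·u·(1 − w0 − d). Relative change = −d/(1 − w0), whatever u is.
- For d = 0.10: 0.10/0.95 = 10.5%, 0.10/0.90 = 11.1%, 0.10/0.80 = 12.5%.
- With u = 0.5 and w0 = 0.10, the counts are 30,000 × 0.5 × 0.90 = 13,500 and 30,000 × 0.5 × 0.80 = 12,000.
- For d = 0.01: 0.01/0.95 to 0.01/0.80, or 1.05% to 1.25%.

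**4. Would a denominator of treated patients cure it?** Not fully. In step 2 the share recorded among those treated goes from 22,500/30,000 = 75.0% to 21,750/28,500 = 76.3%. In step 3, assume also that half of recorded patients are adequately treated and withdrawn at w0, and all others are withdrawn at w0 + d. With u = 0.5, w0 = 0.10 and d = 0.10, the unrecorded share is 0.400/(0.400 + 0.200 + 0.225) = 48.5%, against 50.0% in control. Over u from 0.3 to 0.7 and w0 from 0.05 to 0.20, the shift is 1.2 to 1.7 points. At d = 0.01 it is only about 0.11 to 0.16 points.

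**5. Detectability.** Sample size states a detectable difference of 1%, but does not tie it to REGISTER and gives neither a base rate nor an intracluster correlation. With 27,000 per arm after 10% loss, 90% power and two-sided 5%, the detectable difference is 3.24 × √(2p(1 − p)·DE/n). Without clustering (DE = 1) this is 0.84 to 1.39 points for base rates p of 10% to 50%. At an assumed intracluster correlation of 0.01 (about 199 patients per centre, DE = 2.98) it is 1.45 to 2.41 points. The stated 1% can be neither confirmed nor refuted.

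**The case against.** Four objections have weight.

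- **Ever treated is a natural reading.** Under Study population, patients enter on receipt of a new prescription, and no exit on withdrawal is described. On that reading withdrawals remove nobody and the figures in step 3 vanish. This stands. Avoided starts remain under either reading, diluted if both years are pooled.
- **The definition may be a slip.** The article counts patients without a record yet expects REGISTER to rise, and the abstract treats it as recording itself. If a count of recorded patients was meant, losing an unrecorded patient would not lower it, and the count figures above would not apply. That is a fair caution. But the written definition is explicit, and it needs correcting on this ground too. Turning it into a share of treated patients would not fully help (step 4).
- **Recording can be analysed in other ways.** Under Other variables, recorded cardiovascular risk is collected for each patient. A reader might infer that the trial cannot separate recording from prescribing at all. The document does not support that: the data are there, and the fault lies in the index chosen.
- **Denominators and time windows are often left to the full protocol.** True, and their absence alone is not the point. The point is that the stated definition requires statin treatment.

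Two further inferences are tempting and unsupported. One is that every treatment withdrawn or prevented leaves REGISTER; the table in step 1 shows otherwise. The other is that the artefact exceeds what the trial can detect; step 5 shows that this is not established.

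**Conclusion.** The concern holds in limited form. As defined, REGISTER can differ between arms with no difference in risk recording, because being counted requires statin treatment and the intervention aims to reduce inadequate treatment. It does not isolate objective 4.

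The size is illustrative. The count falls by 10.5% to 12.5% for 10 points more withdrawal among unrecorded patients, assuming control withdrawal of 5% to 20%, currently-treated status and identical recording. For 10% of inadequate starts avoided, it falls by 10% in the feedback year, or 5% if both years are pooled. The rates of recording, withdrawal and adequacy behind these figures are assumptions, since the article gives none of them.

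One secondary outcome is affected; the primary outcomes are not. The definition should be changed, also because its expected direction contradicts it.

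**What to change.** Assess objective 4 in a cohort fixed before feedback starts:

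- **Cohort:** all eligible primary-prevention patients whose new treatment began between 1 October 2011 and 30 September 2012, each kept in the denominator whether or not treatment later stops.
- **REGISTER:** the proportion with any cardiovascular risk calculation in ECAP by 30 September 2013, adjusted for whether a record existed at 1 October 2012. A similarly focused alternative is the proportion newly recorded among those unrecorded at that date. Either way, a patient whose risk was properly recorded at initiation is not treated as a recording failure.
- **Analysis:** compare arms with the multilevel logistic model already planned under Statistical analysis.

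A rise then means more recording, which agrees with the increase the article expects. The abstract's description should be aligned with the new definition.

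The cost is the redefinition of one secondary outcome. No new data are needed: recorded risk is already a study variable, and the dates of treatment start and risk calculation are already needed for the adequacy criteria. The downside is that patients who start in the feedback year are not covered, although recording around initiation could change in them too. They should be described separately. The existing count can stay as a descriptive measure of patients treated without a record.

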### Study population

Twelve PCC are excluded because their current participation in a different intervention could invalidate the results of this study. The research team will identify all patients aged 35 to 74 years who received a new prescription for cholesterol-lowering drugs from the remaining 271 PCC during the study period (October 1, 2011-September 30, 2013), as recorded in the electronic medical records system, known as ECAP. Exclusion criteria are any history of cardiovascular disease (ischemic heart disease, cerebrovascular accident, or peripheral artery disease) recorded in ECAP and patients for whom pharmacy records showed receipt of a cholesterol-lowering prescription drug during the 12 months preceding their inclusion in the study.

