### Intervention design

Based on the list of patients with inclusion and exclusion criteria, the research team will analyze the adequacy of new prescriptions for cholesterol-lowering drugs, based on the recommendations contained in ICS clinical practice guidelines on cholesterol and coronary risk [26]. The flow chart for this analysis is included as Additional file 1.

All GPs assigned to the intervention group will receive informational feedback about the adequacy of cholesterol-lowering drugs prescribed for their patients. Feedback is provided as part of the ECAP system capabilities. The preparation and dissemination of intervention-related feedback will be monthly, beginning in the second year of the study (October 1, 2012-September 30, 2013). This information, available to the GPs at their convenience, will be presented in two distinct and complementary formats and updated throughout 12 consecutive months:

1. Asynchronous information (patient not present)

a) Quantitative information about the percentage of the GP’s assigned patients who have started primary cardiovascular prevention therapy with cholesterol-lowering drugs and that is considered correctly indicated according to the criteria established in the corresponding ICS clinical practice guidelines [26].

b) List of names of patients who have started primary cardiovascular prevention therapy with cholesterol-lowering drugs but do not meet the guidelines criteria.

2. Real-time information (patient present when information is presented to GP).

3. In each GP’s daily schedule, an alert symbol will indicate appointments with patients who have started statins therapy for primary cardiovascular prevention without meeting the established indications criteria. In addition, a message will be included in the ECAP system of clinical advisories. This screen, used during the patient visit, shows all active clinical advisories and alerts for that specific patient. This may include EQA information, medication safety considerations, notice of availability of test results, etc.

The GPs assigned to the control group will not receive the project’s ECAP feedback. The study algorithm is diagrammed in Additional file 2.

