### Outcomes

New treatment with cholesterol-lowering drugs is defined as a prescription given to a patient who has not collected any such prescription from a pharmacy during the 12 months preceding study inclusion, according to national health system records.

Primary prevention is considered the absence of cardiovascular disease (ischemic heart disease, cerebrovascular accident, peripheral artery disease).

The ICS clinical practice guidelines on cholesterol and coronary risk are applied to determine prescription adequacy when cholesterol-lowering drugs are prescribed for primary prevention [26]. To operationalize the algorithm, adequate treatment is defined as meeting one or both of the following criteria:

A. At least 10% cardiovascular risk, according to REGICOR 10-year risk calculated within 12 months of treatment initiation. The REGICOR risk function has been calibrated and adapted to local incidence and distribution of risk factors in Catalonia [27]. It stratifies cardiovascular risk into 4 classifications: low (<5%), moderate (5%–9.9%), high (10%-14.9%), and very high (>15%). The ICS clinical practice guidelines recommend the use of REGICOR tables to calculate coronary risk and consider individuals with at least 10% risk of a 10-year coronary event to be candidates for more intensive interventions, which may include cholesterol-lowering drugs. Additional file 3 contains the REGICOR risk tables, adapted from the Framingham risk calculation.

B. At least 240 mg/dl LDL cholesterol recorded during the 12 months preceding treatment initiation.

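### REGISTER accepts a risk calculation of any date, so old records dilute the arm difference that secondary objective 4 is meant to measure

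*Protocol article*

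**What the plan says.** Under Secondary outcomes, the protocol article defines REGISTER as the number of primary-prevention patients "treated with statins without having any record of a cardiovascular risk calculation". It gives no window for the calculation and no assessment date.

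The objective it serves is item 4 under Secondary objectives: "To analyze the degree to which cardiovascular risk is recorded in electronic medical records after the intervention". Under Intervention design, feedback is given only in the second study year, 1 October 2012 to 30 September 2013.

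The neighbouring definitions do carry time limits. Criterion A for adequacy, under Outcomes, reads: "At least 10% cardiovascular risk, according to REGICOR 10-year risk calculated within 12 months of treatment initiation". RETIRA, EVITA and COST are each tied to a stated period.

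Under Study population, the trial takes "all patients aged 35 to 74 years who received a new prescription for cholesterol-lowering drugs from the remaining 271 PCC during the study period", and excludes "patients for whom pharmacy records showed receipt of a cholesterol-lowering prescription drug during the 12 months preceding their inclusion in the study".

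The Methods part of the abstract describes a different quantity: "REGISTER, defined as the recording of cardiovascular risk factors".

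**The concern.** An outcome for recording after the intervention should be able to change when a GP records a risk calculation after the intervention. REGISTER cannot do so for anyone who already has a calculation on file, however old. According to Data collection and follow-up, the record system has been in routine use in all centers since 2005, so a qualifying record could be about seven years old when feedback starts (2012 − 2005 = 7).

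The affected patients include some whom the feedback targets. If the only calculation on file falls outside the 12-month window, it does not count towards adequacy. Unless the LDL criterion is met, the patient is then classed as inadequate and appears in the feedback. If the GP responds by recalculating risk, REGISTER does not register it.

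The risk is that a real effect of feedback on risk recording is understated, or reported as absent.

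**Working it through.** The article states no rate, effect or sample size for REGISTER, so there is no figure of the plan's own to reproduce. The check has two parts.

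**1. One patient followed through the definitions (hypothetical dates)**

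- 2008: risk calculated and recorded.
- February 2012: new cholesterol-lowering prescription; no later risk calculation; no LDL of 240 mg/dl or more in the preceding 12 months.
- Adequacy (Outcomes): the 2008 value is outside the 12-month window, so the treatment is inadequate.
- Feedback (Intervention design): in the intervention arm, the patient is listed and flagged from October 2012.
- November 2012: the GP recalculates risk.
- REGISTER: recorded before November 2012 and recorded after it. No change.

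**2. Size of the dilution**

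Inputs:

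- q = share of the REGISTER population with a calculation from before the intervention. Not in the documents; assumed 30% to 60%, with 0% for reference. Taken as equal in the two arms because of randomization.
- Among patients without such a record, the share who get a calculation: 20% in control and 30% in intervention. Not in the documents; chosen only to illustrate a difference of 10 points.

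Formulas:

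- Control, no record: (1 − q) × 0.80
- Intervention, no record: (1 − q) × 0.70
- Arm difference: (1 − q) × (0.70 − 0.80) = (1 − q) × (−0.10)
- Odds ratio for no record: [I / (1 − I)] ÷ [C / (1 − C)], where I and C are the two no-record proportions

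| q | C | I | Difference, points | Ratio I/C | Odds ratio |
|---|---|---|---|---|---|
| 0 | 0.80 | 0.70 | −10.0 | 0.875 | (0.70 × 0.20)/(0.30 × 0.80) = 0.583 |
| 0.30 | 0.56 | 0.49 | −7.0 | 0.875 | (0.49 × 0.44)/(0.51 × 0.56) = 0.755 |
| 0.60 | 0.32 | 0.28 | −4.0 | 0.875 | (0.28 × 0.68)/(0.72 × 0.32) = 0.826 |

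The absolute difference is multiplied by 1 − 0.30 = 0.7 to 1 − 0.60 = 0.4. The ratio of no-record proportions is unaffected, because (1 − q) cancels. The odds ratio moves towards 1. That matters if REGISTER is analysed like the main outcomes, since Statistical analysis names multilevel logistic regression for the intervention effect; the article does not say which model REGISTER will get.

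**The case against.** Four points can be made for the plan.

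- **Different questions may use different windows.** REGISTER can be read as asking whether risk was ever calculated, and adequacy as asking whether a recent value justifies treatment. Being recorded for one and inadequate under the other is then no contradiction. This stands as logic, but ever-recorded is not what objective 4 asks.
- **An article condenses.** Look-back windows are often left to a fuller document. Here, though, the article does not stay silent: it sets a criterion that accepts a record of any date, next to outcomes for which it states periods.
- **Randomization balances old records.** This stands. A reader might infer that REGISTER cannot measure the effect at all, or that old records dominate it. Neither is supported: the expected contrast shrinks but keeps its direction, and no figure for q is given.
- **The population is restricted elsewhere.** Because REGISTER speaks of patients treated with statins and omits the word new, a reader might infer that long-standing users swamp it. Study population rules this out: it admits only new prescriptions and excludes anyone who received such a drug in the previous 12 months. At most, people restarting after a longer gap could enter. What remains is a wording gap.

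**Conclusion.** The concern holds as a mismatch between an undated outcome and an objective about recording after the intervention. Patients in the new-start population with an old calculation cannot change status, so the absolute arm difference is (1 − q) times the difference among the rest. For an assumed q of 30% to 60% the factor is 0.7 to 0.4, and a difference of 10 points would show as 7 to 4 points.

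This rests on q being similar in the two arms. The true q is unknown from the documents, so the loss could be smaller or larger than this range. The outcome is secondary, and the primary outcomes RETIRA and EVITA do not depend on this definition.

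**What to change.** - **Confirmatory comparison.** Define REGISTER on first-year new starts (1 October 2011 to 30 September 2012) who, as of 1 October 2012, have no valid risk calculation under the window in adequacy criterion A. The measure is the proportion with a risk calculation dated 1 October 2012 to 30 September 2013, compared by arm. This cohort is fixed before feedback begins, so the intervention cannot alter who is in it. A proportion with a calculation also rises when recording improves, which fits the increase that the article expects; the present count of patients without a record would fall.
- **Second-year starts.** Report recording among them descriptively only. Starting treatment is itself something the intervention aims to change (EVITA), so an arm comparison among starters conditions on an affected variable.
- **Population.** State that REGISTER applies to the new-start population of Study population.
- **Abstract.** Replace the reference to risk factors with risk calculation.

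Cost: a change of wording and a date filter on data already to be extracted. The downside is that fewer patients contribute to the measure. Some dilution remains from first-year starts who are adequate through the LDL criterion alone, since they trigger no patient-specific alert; they can be identified from data before the intervention and set aside in a sensitivity analysis.

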### Statistical analysis

Initially, descriptive analysis will be completed for all study variables: mean (standard deviation) for continuous variables with a normal distribution, median (interquartile ranges) in the case of non-normal distribution and the frequency (percentage) of categorical variables. Differences between the intervention and control groups will be assessed using the χ2 or Fisher exact test for categorical variables and Student *t* for continuous variables with normal distribution, or nonparametric Mann–Whitney U test, as appropriate. Differences between means, medians, or ratios at the beginning and end of the two-year follow-up period (pre- and post-intervention) will be compared using the McNemar test, Student *t* for paired tests, or Wilcoxon test, as appropriate.

The percent change with respect to baseline value is used as a measure of the pre- and post-intervention change in categorical variables, calculated as the final percentage minus the initial percentage × 100.

The intervention effect after one year of follow-up will be evaluated using the decrease in the EVITA variable and increase in the RETIRA variable. To assess the effect of the intervention model, a multilevel logistic regression analysis will be performed, considering intervention vs control group as the independent variable. The analysis will be adjusted for potential predictive independent variables and, for those considered clinically relevant, for baseline values.

To determine the economic impact of new prescriptions of cholesterol-lowering drugs in primary prevention prescribed during the study period, a descriptive analysis of costs and resource use will be completed for each study group and the groups will be compared (discount rate: 3%). The incremental cost-effectiveness ratio will be calculated as the difference between the cost average for the 2 study groups, divided by the difference between the effects for both groups. Acceptance curves will be calculated to determine the cost-effectiveness of the intervention compared to usual practice.

Significance will be established at the 5% level. All analysis will be done using Stata/SE, version 10.1 (StataCorp).

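### REGISTER is defined as a count of patients without a recorded risk calculation, yet success is stated as an increase; the COST window also needs stating

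*Protocol article*

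**What the plan says.** **REGISTER.** The Secondary outcomes section of the protocol article opens with the purpose: "To assess the recording of cardiovascular risk in electronic medical records, the REGISTER variable will be calculated". The definition that follows is the number of patients without cardiovascular disease who are "treated with statins without having any record of a cardiovascular risk calculation". The section closes with the expected direction: "The intervention is designed to produce an increase in the REGISTER variable and a decrease in the COST variable". The Methods paragraph of the abstract has "REGISTER, defined as the recording of cardiovascular risk factors". Secondary objective 4, which this outcome serves, reads "To analyze the degree to which cardiovascular risk is recorded in electronic medical records after the intervention".

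**COST.** The same section defines COST as the total cost of new primary-prevention prescriptions "reimbursed by the national health system that are considered inadequate during the study period". Study population fixes the term: "during the study period (October 1, 2011-September 30, 2013", which is 24 months. Intervention design starts the feedback only in the second of those years, on October 1, 2012. The abstract, however, places the EVITA starts in the study period, while Primary outcomes places them in the 12-month follow-up.

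**The concern.** An outcome's definition and its success direction must point the same way. Here the definition counts failures to record, and the stated target is for that count to rise. An analyst who programs the Methods definition and then reads off the stated direction would report improved recording as movement the wrong way.

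A second weakness would survive a simple change of sign. REGISTER is a number of patients, with no denominator in its definition. The intervention is meant to reduce inadequate starts and to prompt withdrawals, so the number treated should differ between arms, and the count will follow it even if recording habits do not change.

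For COST, a total over both years includes a year in which neither arm received feedback. That weakens any relative reduction reported.

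**Working it through.** The document gives no figure for REGISTER or COST, so there is none to reproduce. The recording shares, patient numbers and accrual patterns below are assumptions for illustration.

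**1. Direction of REGISTER.** Let T be the number of treated patients and p the share with a risk calculation on record. As defined, REGISTER = T × (1 − p).

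| Scenario (T = 1,000) | REGISTER as defined | Patients with a record |
|---|---|---|
| p = 50% | 1,000 × 0.5 = 500 | 500 |
| p = 60% | 1,000 × 0.4 = 400 | 600 |
| p = 70% | 1,000 × 0.3 = 300 | 700 |

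The stated target is an increase. The variable as defined falls as recording improves; its complement rises. Withdrawal moves it the same way: stopping treatment in 10% of the 500 unrecorded patients gives 500 × 0.9 = 450.

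**2. Why a count is not enough.** Suppose 1,000 starts in the control arm and 800 in the intervention arm, with 50% recorded in both. The count without a record is 500 against 400, and the count with a record is also 500 against 400. Either count suggests a difference of 100 where recording is the same. The proportion is 50% in both arms.

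**3. COST over 24 months.** Let r be the true relative cut in intervention-year cost and s the share of the control arm's 24-month cost that falls in that year. The apparent cut over 24 months is r × s.

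- Equal cost in each year: s = 1/2.
- Uniform accrual with full persistence: year-1 starters contribute on average 0.5 treatment-years in year 1 and 1 in year 2, and year-2 starters contribute 0.5 in year 2. So s = 1.5/2 = 0.75.

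| True cut in intervention year | Apparent cut, s = 0.5 | Apparent cut, s = 0.75 |
|---|---|---|
| 10% | 5% | 7.5% |
| 20% | 10% | 15% |
| 30% | 15% | 22.5% |

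Write C1 and C2 for the expected control cost in the two years. Randomization makes C1 equal in expectation in both arms, so the absolute difference is (C1 + C2) − (C1 + C2(1 − r)) = r × C2, the same as for year 2 alone. The extra year adds noise but no bias to that difference.

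**The case against.** The best defence on REGISTER is that the intent is plain. The opening of its own definition, the abstract and objective 4 all speak of recording, so a careful analyst would see a slip and reverse it. That stands as a limit on the damage. It does not remove the contradiction, which sits in the current Methods text between the operational definition and the success criterion.

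On the denominator, Statistical analysis says that categorical variables will be summarized as frequency and percentage and that change will be measured in percentages. That is a fair pointer towards a proportion. But the definition says a number, and it does not say of whom the percentage would be taken.

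On COST, the abstract's use of the same term for the EVITA window leaves a 12-month reading open, and the article does not say that a relative reduction will be reported. Objective 5 also asks for economic impact over the study period, for which year-1 data are legitimate. All of this stands, and it makes COST a minor point about an inconsistently used term.

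A reader might go further and infer that the cost-effectiveness ratio is circular, with COST over inadequate prescriptions avoided merely returning a unit price. The document does not support this. The ratio is "calculated as the difference between the cost average for the 2 study groups, divided by the difference between the effects for both groups". Neither COST as the cost nor inadequate prescriptions avoided as the effect is named, and the same section refers to costs and resource use of new prescriptions, not only inadequate ones.

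**Conclusion.** The REGISTER definition contradicts its stated direction, the abstract and objective 4. This is an error in a secondary outcome and should be corrected before analysis. Read literally, every improvement in recording moves the variable against its target; the size depends on the assumed recording shares (500 to 400 per 1,000 for a 10-point gain). As a raw count it also confounds recording with the number of patients treated.

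It would be too strong to infer that the trial as a whole would call an effective intervention a failure. RETIRA and EVITA are defined without REGISTER and are unaffected, and the intended meaning can be recovered from the rest of the article.

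The COST window is a minor ambiguity. On the 24-month reading a 20% cut in the intervention year appears as about 10% to 15% under the two assumed accrual patterns, with added noise but no bias in the absolute difference. No fault in the cost-effectiveness ratio is established.

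**What to change.** 1. Define REGISTER as the proportion of new primary-prevention starts with a recorded cardiovascular risk calculation, with an increase as success. Report the numerator and denominator by arm, because the intervention may also change who starts treatment.
2. Align the abstract with the Secondary outcomes section. The abstract speaks of risk factors where the Methods speak of a risk calculation; use the latter in both.
3. State that the between-group COST comparison covers costs incurred from October 1, 2012 to September 30, 2013, including those of treatments begun in year 1 that continue into it. Restricting COST to new starts in that year would lose the savings from withdrawal. A 24-month total can remain as a description for objective 5.
4. Use the term study period for one window only.

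The cost is wording. Recorded risk is already a listed patient variable, and the pharmacy records already hold dispensing with its cost, so no new data are needed.
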